### Secondary outcome measures

Episodes of apnea, defined as the need for sustained stimulation to initiate breathingSepsis, defined as the presence of at least two of the following clinical signs: lethargy, persistent apnea, poor feeding; feverMortality before hospital dischargeIn-hospital growth, defined as weight at discharge

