**Methods/design:**

This is a multicenter (three hospitals), multicountry (three countries), prospective, unblinded, randomized controlled trial of KMC treatment with and without a woolen cap in LBWI. After obtaining parental consent, all infants with a birth weight below 2500 g and who are candidates for KMC, based on the clinical decision of the attending physician, will be assigned to the KMC with a woolen cap group or to the KMC without a woolen cap group in a 1:1 ratio according to a computer-generated, randomized sequence. The duration of the study will be until the patient’s discharge, with a maximum treatment duration of 7 days.

The primary outcome measure will be whether the infants’ temperatures remain within the normal range (36.5–37.5 °C) in the course of KMC during the intervention. In all participants, axillary temperature will be measured with a digital thermometer four times per day. In addition, maternal and room temperature will be recorded.

Secondary outcome measures will be: episodes of apnea; sepsis; mortality before hospital discharge; in-hospital growth; and age at discharge.

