### Inclusion criteria

Infants satisfying the following inclusion criteria will be eligible to participate in the study:Birth weight below 2500 g (and)Candidate to KMC treatment (and)Parental consent: a written informed consent will be obtained by a member of the neonatal team involved in the study from a parent or guardian before KMC treatment

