### Procedure

After obtaining parental consent, all infants with a birth weight below 2500 g and who are candidates for KMC, based on the clinical decision of the attending physician, will be assigned to the KMC with a woolen cap group (KMC + cap) or to the KMC without a woolen cap group (KMC group). All the caps used for the study are handmade by a group of volunteers in Padova. The material (wool) was provided by CUAMM and sizes were standardized.

The procedure of initiating, maintaining and stopping the KMC will be based on WHO guidelines [5]. Mothers will be trained in monitoring the baby’s condition and in recognizing dangerous clinical signs during KMC [5]. The duration of the study will be until the patient’s discharge, with a maximum treatment duration of 7 days. In case of documented neonatal hypothermia (temperature below 36.5 °C) or hyperthermia (temperature above 37.5 °C) during the course of the study, the pre-warmed blanket will be added or removed. In case of maternal hyperthermia, we will ask the woman to wear lighter clothes. In these cases, neonatal and maternal temperatures will be measured every hour until the normal range is reached.

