### Statistical analysis

Analysis will be performed as per intention-to-treat. Continuous data will be expressed as mean and standard deviation (SD) or median and interquartile range (IQR). The effect of the treatment on primary outcome will be assessed using a Poisson model adjusting for hospital and a set of clinically relevant confounders (maternal temperature, environmental temperature, birth weight, postnatal age). The logarithm of the number of measurements during hospital stay will be used as an offset, in order to take into account the different lengths of hospital stay of each participant. The effect of the treatment on the number of episodes of apnea will be assessed using a Poisson model adjusting for hospital and a set of clinically relevant confounders (neonatal and maternal temperatures, environmental temperature, birth weight, postnatal age). The logarithm of the number of measurements during hospital stay will be used as an offset. The effect of the treatment on binary secondary outcome (sepsis and mortality before hospital discharge) will be assessed using a logistic regression model adjusting for hospital and birth weight. The effect of the treatment on continuous secondary outcome (in-hospital growth) will be assessed using a regression model adjusting for hospital. Statistical analysis will be performed using R 3.2.2 software (R Foundation for Statistical Computing, Vienna, Austria) [11]. A *p* value less than 0.05 will be considered statistically significant.

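### In-hospital growth is defined as raw discharge weight and modelled without birth weight: the arm comparison stays unbiased, but it measures attained size and loses precision

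*Protocol article*

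**What the plan says.** Under Secondary outcome measures, the protocol article gives the outcome as "growth, defined as weight at discharge". No starting weight and no elapsed time enter the definition.

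Under Statistical analysis, the "continuous secondary outcome (in-hospital growth) will be assessed using a regression model adjusting for hospital". No other covariate is named for this outcome.

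The other models in the same paragraph all carry birth weight:
- The primary Poisson model adjusts for hospital and for "maternal temperature, environmental temperature, birth weight, postnatal age".
- The apnea model uses the same set plus neonatal temperature.
- Sepsis and mortality use a "logistic regression model adjusting for hospital and birth weight".

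Birth weight must be known at entry, since the first inclusion criterion is "Birth weight below 2500 g". No lower limit is set. Randomisation is 1:1 with a separate sequence for each hospital, and no stratification by birth weight is stated. Follow-up runs "until the patient’s discharge, with a maximum treatment duration of 7 days".

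The abstract ends its list of secondary outcomes with "in-hospital growth; and age at discharge". Age at discharge does not appear in the methods list of secondary outcomes or in the analysis section.

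**The concern.** Growth means change in weight. Weight at discharge is a size, made up of what the infant weighed at birth plus what was gained or lost since. The cap is used for at most 7 days, so any effect on weight is likely to be small against the spread of birth weight among infants admitted anywhere below 2500 g. A model that leaves birth weight out puts that spread into the residual and widens the confidence interval for the cap effect.

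The choice also looks unintended: growth is the only modelled outcome without birth weight, and probably the one that birth weight would explain best.

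At stake is the reading of one secondary outcome. An inconclusive result could be taken as evidence that the cap does not affect growth, when the analysis could not have shown a modest effect. A chance difference in birth weight between the arms could also be read as a difference in growth.

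**Working it through.** **No figure of the plan's own to reproduce.** The Sample size section says that 300 was set arbitrarily, and it gives no effect size, SD or power. Its totals agree: 150 + 90 + 60 = 300 by hospital and 150 + 150 = 300 by arm.

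**Inputs.** From the protocol: 150 infants per arm and a significance level of 0.05 (two-sided assumed). Assumed, because the protocol gives none: SD of birth weight (SDb) 200 to 400 g, SD of gain (SDg) 60 to 200 g, and correlation r between birth weight and gain from −0.3 to 0.3. The central case is 300 g, 100 g and 0.

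**Formulas.** Discharge weight = birth weight + gain, so:
- Planned model: residual variance = SDb² + SDg² + 2·r·SDb·SDg
- With birth weight added: residual variance = SDg²·(1 − r²)
- Difference detectable with 80% power = (1.960 + 0.842) × residual SD × √(2/150)
- Variance penalty = planned residual variance ÷ adjusted residual variance

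These treat the spread as that remaining after hospital is in the model.

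**Central case.**
- Planned: √(300² + 100²) = √100,000 ≈ 316 g. Detectable difference 2.802 × 316 × 0.1155 ≈ 102 g.
- Adjusted: residual SD 100 g. Detectable difference 2.802 × 100 × 0.1155 ≈ 32 g.
- Penalty: 100,000 ÷ 10,000 = 10. Birth weight explains 1 − 1/10 = 90% of the variance, and 300 infants analysed as planned are worth about 300/10 = 30 analysed with birth weight.
- Power for an illustrative 50 g difference: about 28% planned, about 99% adjusted.

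**Range over the grid.**

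| Case (SDb, SDg, r) | Planned residual SD | Adjusted residual SD | Variance penalty |
|---|---|---|---|
| 200, 200, −0.3 (smallest penalty) | 237 g | 191 g | 1.5 |
| 300, 100, 0 (central) | 316 g | 100 g | 10 |
| 400, 60, 0.3 (largest penalty) | 422 g | 57 g | 54 |

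Across the whole grid, birth weight explains 35% to 98% of the variance. The detectable difference is 62 to 161 g as planned and 19 to 65 g with adjustment.

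**Bias and type I error.** In 4,000 simulated trials with no cap effect, central-case SDs and 1:1 allocation within hospitals of 150, 90 and 60 infants:
- Planned model: mean estimate −0.3 g, SD of the estimate 36.7 g, type I error 0.049.
- With birth weight added: mean estimate 0.0 g, SD 11.4 g, type I error 0.043.

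Both are centred on zero and neither exceeds the nominal error rate. The planned estimate is about three times as variable (36.7 ÷ 11.4 ≈ 3.2).

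**Response after adjustment.** If discharge weight = a + τ·arm + hospital + β·birth weight, subtracting birth weight from both sides gives gain = a + τ·arm + hospital + (β − 1)·birth weight. The cap effect τ and its standard error are identical, so once birth weight is in the model it does not matter whether discharge weight or gain from birth is the response.

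**The case against.** A reader might infer that the comparison mainly measures how big the infants were at birth, and so is biased. The documents do not support that. Allocation is randomised 1:1 within hospital, so birth weight is balanced in expectation, and the simulation shows an unbiased estimate with type I error held. A chance imbalance in birth weight is ordinary sampling error, which the standard error already reflects. Birth weight may dominate the variation between infants, but it does not distort the treatment contrast.

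The size of the loss rests wholly on assumed figures. If smaller infants stay longer before discharge, discharge weight could follow birth weight less closely. This objection stands, and it is why a wide range is given. Only the direction is secure: the penalty exceeds 1 throughout the grid.

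A reader might also infer that every variable needed for a fuller repair is already collected. That is shown for birth weight but not for age at discharge. The Data collection section points to the items listed under the primary and secondary outcomes, and age at discharge is not among them. Nor does the gap mean that age at discharge was abandoned, since the abstract still names it.

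It cannot be argued that the choice is left to a fuller document. The protocol article fixes both the definition and the covariate for this outcome.

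**Conclusion.** The point holds as a matter of labelling and precision. The outcome called growth is attained weight, and its model omits the one baseline variable that most plausibly explains it, although that variable is known for all infants and used in every other outcome model. In the central case the detectable difference is about 102 g where about 32 g was attainable. The variance penalty is about 10 times there and about 1.5 to 54 times over the assumed grid. All of these figures depend on SDs and correlations that the protocol does not give.

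No bias and no inflation of type I error follow. This is one secondary outcome in a trial without a power claim, and the primary model already includes birth weight, so the main conclusion is untouched. The mismatch over age at discharge is a separate and smaller inconsistency between the abstract and the methods.

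**What to change.** In Statistical analysis, add birth weight to the growth regression alongside hospital (ANCOVA). In Secondary outcome measures and in reporting, describe the result as discharge weight adjusted for birth weight rather than as growth. This changes wording and one model term. It needs no new data, no further infants and no change to treatment.

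Gain per day is not an equivalent alternative. It divides by time to discharge, which is determined after randomisation and might be affected by the cap. Counted from birth, it also includes time before the infant was randomised.

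Separately, reconcile the abstract, which lists age at discharge, with the methods list and the analysis section, which omit it: either restore it in both places with a stated analysis or remove it from the abstract with a reason. Before restoring it, confirm that the discharge date is on the data sheet. If it is, this too costs only wording; if not, one field has to be added or retrieved from hospital records.

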### Generalizability

The findings of this study will be important for other units/settings in high- as well low-resource countries where KMC is routinely performed. Based on the results of the present study, we could speculate whether the use of a woolen cap may help to maintain the neonate within the normal thermal range. Furthermore, potential complications such as hyperthermia will be strictly monitored and collected.

### Sample size

The lack of information about this topic (temperature during KMC in the specific scenario of head covering) prevented us from obtaining a mathematical estimation of the sample size. Thus, the sample size was arbitrarily defined in order to take into account the enrollment rate of each hospital. According to the number of admissions in each participating hospital, we decided to enroll a total of 300 subjects (150 in the cap group and 150 in the uncovered head group) as follows: 150 at Central Beira Hospital, 90 at St. Luke Wolisso Hospital and 60 at Aber Hospital.

### Recruitment

Written and oral information will be offered to parents by the attending nurse or physician prior to starting KMC treatment. Informed written consent will be signed by a parent. A senior investigator will be available at all times to discuss concerns raised by parents or clinicians during the course of the trial.

### Randomization

Eligible infants will be assigned to the KMC + cap or the KMC group in a 1:1 ratio according to a computer-generated, randomized sequence for each participating hospital. The randomized allocation will be concealed in double-enclosed, opaque, sealed, and sequentially numbered envelopes prepared at the University Hospital of Padua.

In the KMC room, the next sequential randomization envelope will be opened only when the attending operator considers the infant to be eligible. The assigned procedure (KMC + cap or KMC group) will be then performed. Cross-over will not be allowed. Analysis will be done as per intention-to-treat. A flow diagram of patient randomization is reported in Fig. 1.

**Fig. 1 Fig1:**
[figure not shown]
Flow diagram of patient randomization

### Blinding

Due to the characteristics of the intervention, neither caregivers nor outcome assessors will be masked to treatment allocation. However, the statistician who will perform data analysis will be blind to treatment allocation. To minimize bias, strict criteria and definitions will be maintained during the trial.

### Guidelines for management

Before starting the study, all those involved in the study will participate in a meeting where all the details of the study will be presented. Midwives and nurses who are responsible of the maternal and neonatal management during KMC treatment will be educated on the temperature measurements in terms of correct modality (axillary), time of the study, and data collection. Neonatal, maternal and room temperature will be collected four times/day (6.00 am, 12.00 am, 6.00 pm, and 12.00 pm).

### Data collection

Data will be recorded in a data sheet designed for this study. All data will be collected by an observer who is not involved in the care of the neonates. The following clinical information will be registered: eligibility, antenatal history, randomization, all data above listed in the ‘Primary outcome measure’ and ‘Secondary outcome measures’ sections. Further information will be collected on expected serious adverse events (SAEs). Personal information about potential and enrolled participants will be collected, shared, and maintained in order to protect confidentiality before, during, and after the trial by the local principal investigator (PI) in a personal password-protected PC. The PI and the members of the Steering Committee located in Padua will have access to the final trial dataset.

### Statistical analysis

Analysis will be performed as per intention-to-treat. Continuous data will be expressed as mean and standard deviation (SD) or median and interquartile range (IQR). The effect of the treatment on primary outcome will be assessed using a Poisson model adjusting for hospital and a set of clinically relevant confounders (maternal temperature, environmental temperature, birth weight, postnatal age). The logarithm of the number of measurements during hospital stay will be used as an offset, in order to take into account the different lengths of hospital stay of each participant. The effect of the treatment on the number of episodes of apnea will be assessed using a Poisson model adjusting for hospital and a set of clinically relevant confounders (neonatal and maternal temperatures, environmental temperature, birth weight, postnatal age). The logarithm of the number of measurements during hospital stay will be used as an offset. The effect of the treatment on binary secondary outcome (sepsis and mortality before hospital discharge) will be assessed using a logistic regression model adjusting for hospital and birth weight. The effect of the treatment on continuous secondary outcome (in-hospital growth) will be assessed using a regression model adjusting for hospital. Statistical analysis will be performed using R 3.2.2 software (R Foundation for Statistical Computing, Vienna, Austria) [11]. A *p* value less than 0.05 will be considered statistically significant.

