### Primary outcome measure

The primary outcome measure will be whether the infants’ temperatures remain within the normal range (36.5–37.5 °C) in the course of KMC during the intervention. In all participants, axillary temperature will be measured with a digital thermometer (C202; Terumo, Tokyo, Japan) every 6 hours during KMC treatment. Maternal and room temperature will be registered at the same time. Room temperature will be measured at the same times (every 6 hours) by using the same wall thermometers (Oregon Scientific RMR262) in all three study sites.

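### The primary Poisson model assumes a variance that a bounded count of correlated readings does not have, so its type I error is not controlled at 5% and may lie well above or below it

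*Protocol article*

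**What the plan says.** All references are to the protocol article.

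- **Outcome** (Primary outcome measure): whether an infant's "temperatures remain within the normal range" of 36.5–37.5 °C, measured "every 6 hours during KMC treatment".
- **Number of readings**: Guidelines for management states "Neonatal, maternal and room temperature will be collected four times/day". Procedure limits the study to discharge, "with a maximum treatment duration of 7 days". Procedure also adds hourly readings after an abnormal value until it normalises.
- **Model** (Statistical analysis): "The effect of the treatment on primary outcome will be assessed using a Poisson model adjusting for hospital", and for birth weight, postnatal age, and maternal and room temperature. "The logarithm of the number of measurements during hospital stay will be used as an offset", to allow for unequal stays. A p "value less than 0.05 will be considered statistically significant".

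The offset implies one count of readings per infant. The text does not say whether in-range or out-of-range readings are counted, or whether the hourly readings enter the count and the offset. It mentions no robust variance, dispersion term or random effect.

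**The concern.** A Poisson model takes the variance of each count to equal its mean. Two features of this outcome break that equality, in opposite directions. The count is capped by the number of readings, which makes the true variance smaller than Poisson. Readings from the same infant resemble one another, which makes it larger. The two effects cancel only by coincidence.

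Where correlation dominates, model-based standard errors are too small, and the trial could declare a cap effect that is not there. Where the cap on the count dominates, they are too large and power is lost. The second case also matters here, because the Sample size section says that the 300 infants were chosen without a calculation, so there is no planned power margin to absorb a loss.

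**Working it through.** **Inputs from the document.** 300 infants, 1:1, with 150, 90 and 60 by hospital (150 + 90 + 60 = 300); four readings a day for at most 7 days, so m ≤ 4 × 7 = 28 scheduled readings; threshold 0.05, taken as two-sided because no side is stated. The document offers no power figure to reproduce.

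**Assumptions.** The share of readings counted (p), the within-infant correlation (ρ) and the minimum stay are not given. Ranges are shown for p and ρ. The simulation takes stays of 2–7 days, so m = 8–28.

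**Formula.** For m binary readings with common correlation ρ:

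- true variance of the count = m·p·(1−p)·(1+(m−1)ρ)
- Poisson variance with the log(m) offset = m·p
- ratio φ = (1−p)(1+(m−1)ρ)
- actual two-sided error of a nominal 5% test = 2·(1 − Φ(1.96/√φ))

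The error is 5% only when φ = 1, that is, when ρ = p/[(1−p)(m−1)].

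**Worked cases at m = 28**

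- p = 0.5, ρ = 0.1: φ = 0.5 × (1 + 2.7) = 1.85; 1.96/√1.85 = 1.44; error 15.0%.
- p = 0.9, ρ = 0.2: φ = 0.1 × (1 + 5.4) = 0.64; 1.96/0.8 = 2.45; error 1.4%.

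| Share counted, p | Formula, m = 28: ρ = 0.1 / 0.2 / 0.3 | Break-even ρ, m = 28 |
|---|---|---|
| 0.9 | 0.1% / 1.4% / 4.0% | 0.333 |
| 0.7 | 6.3% / 15.7% / 23.6% | 0.086 |
| 0.5 | 15.0% / 27.3% / 35.8% | 0.037 |
| 0.3 | 22.3% / 35.4% / 43.7% | 0.016 |

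**Simulation.** Beta-binomial counts with no treatment effect, 300 infants in the three hospital strata, m = 8–28, log(m) offset, hospital terms and four covariates unrelated to outcome, 600 runs per cell. The Monte Carlo standard error is about 0.9 points at 5%.

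| Share counted, p | Model-based Poisson: ρ = 0 | ρ = 0.1 | ρ = 0.2 | ρ = 0.3 |
|---|---|---|---|---|
| 0.9 | 0.0% | 0.0% | 0.5% | 1.5% |
| 0.7 | 0.0% | 4.5% | 10.2% | 15.7% |
| 0.5 | 0.5% | 11.8% | 22.0% | 29.0% |
| 0.3 | 1.0% | 17.5% | 31.7% | 39.7% |

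The errors are lower than in the formula table because most simulated infants have fewer than 28 readings. With robust (sandwich) standard errors on the same data and point estimate, the error was about 4–7% in every cell run. Quasi-Poisson scaling gave about 4–8.5%.

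**What is counted matters.** The rows for 0.7 and 0.3 can describe the same infants: 70% of readings in range is 30% out of range. Counting one or the other moves the error from 4.5–15.7% to 17.5–39.7%.

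**The case against.** The strongest reply is that the article names no variance estimator. A Poisson model with robust or quasi-likelihood errors fits its wording, and an analysis plan that is not shown may specify one. That stands as a limit: the figures above apply if model-based errors are used. It does not remove the point. The stated distribution and offset do not match the variance of the stated outcome, and the section, which goes as far as covariates and software version, gives no sign of a correction.

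A reader might infer stronger claims that the document does not support:

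- **That the false-positive rate is several times 5%.** Neither p nor ρ is given, and the test is conservative when nearly all readings are counted and are in range. Direction and size are both open.
- **That the simulated inflation would occur in full.** The simulated covariates explained nothing. Real ones could lower the residual ρ. At p = 0.7 and m = 18, moving ρ from 0.2 to 0.1 takes φ from 0.3 × 4.4 = 1.32 to 0.3 × 2.7 = 0.81, and the error from about 9% to about 3%.
- **That readings are analysed as independent rows.** The offset points to one count per infant, so the remaining problem is dispersion.
- **That the apnea model fails in the same way.** Apnea episodes are not a subset of the temperature readings, so the formula does not carry over, and the document has no figures on how episodes cluster.
- **That this test drives the interim stopping decision.** Data Safety and Monitoring Board lists significance on the primary outcome among the stopping criteria after 100 infants, but names no interim model. It also lists a suspected causal link with serious adverse events, and the results are discussed with the board.

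**Conclusion.** The point holds in a two-directional form, for the primary model only. As written, the primary analysis has the stated 5% error only if (1−p)(1+(m−1)ρ) happens to equal 1. For ρ of 0.1–0.3 and 8–28 readings per infant, the type I error runs from about 0–2% when 90% of readings are counted, through 4–16% at 70% and 12–29% at 50%, to 18–40% if out-of-range readings at 30% are counted. These values rest on assumed p, ρ and length of stay, on model-based standard errors, and on covariates that explain none of the variation between infants. The algebra does not depend on the values assumed; the size and direction in this trial cannot be known from the document.

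**What to change.** - Keep the Poisson rate ratio and the offset, but specify infant-level robust (sandwich) standard errors. Alternatively, use a quasi-binomial model of in-range out of total readings per infant. The quasi-binomial option was not simulated here, and with a logit link it reports an odds ratio instead of a rate ratio.
- State whether in-range or out-of-range readings are counted.
- State whether the hourly follow-up readings enter the count and the offset.
- If this model is used at the interim look, use the same variance there.

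The cost is a few sentences of analysis text. No new data are needed, and the methods are available in standard R packages. The downside is that intervals may be wider than the model-based ones, which is the case wherever φ exceeds 1.

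### The apnea model divides episodes by the number of temperature readings rather than by time observed; if the hourly re-readings are counted, the apnea rate ratio can be biased

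*Protocol article*

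**What the plan says.** All references are to the protocol article.

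- **Model and offset (Statistical analysis).** "The effect of the treatment on the number of episodes of apnea will be assessed using a Poisson model adjusting for hospital" and a list of covariates that includes neonatal temperature. The offset is then given: "The logarithm of the number of measurements during hospital stay will be used as an offset". The same offset is used for the primary outcome, where its purpose is stated: "in order to take into account the different lengths of hospital stay of each participant".
- **Scheduled readings.** Axillary temperature is taken "every 6 hours during KMC treatment" (Primary outcome measure). Guidelines for management agrees: "Neonatal, maternal and room temperature will be collected four times/day".
- **Extra readings (Procedure).** After a neonatal temperature below 36.5 °C or above 37.5 °C, "neonatal and maternal temperatures will be measured every hour until the normal range is reached". A raised maternal temperature is also a trigger: "In case of maternal hyperthermia, we will ask the woman to wear lighter clothes", with the same hourly readings.
- **Apnea (Secondary outcome measures).** An episode is defined by the infant needing sustained stimulation to breathe. Nothing links its detection to a thermometer reading. On observation, Procedure says "Mothers will be trained in monitoring the baby’s condition and in recognizing dangerous clinical signs during KMC".

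**The concern.** For the primary outcome, a count of readings is a denominator of the right kind, because an out-of-range temperature can only be found at a reading. Apnea is an event in continuous time, and the matching denominator is the time during which it could occur and be noted.

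The number of readings can stand in for time only if it is proportional to time. The hourly re-readings break that proportion, and they do so through the infant's temperature, which is what the cap is meant to change. The apnea denominator would then be a post-randomization quantity that can differ between arms although apnea per day does not. Better control in the cap arm would make the cap look as if it raised apnea, or hide a true reduction. Worse control, for example through hyperthermia, would make it look protective. Apnea is the first-listed secondary outcome and bears on safety, so an error in either direction matters.

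**Working it through.** The protocol states no apnea rate, rate ratio or power for this outcome, so there is no figure of its own to reproduce.

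**Inputs from the protocol:** 4 scheduled readings a day, hence at most 4 × 7 = 28 in the 7-day treatment period; hourly re-readings until the range is regained; 300 infants, 1:1.

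**Inputs assumed, because the protocol does not give them:** p, the share of scheduled readings out of range; k, the mean number of hourly re-readings per out-of-range reading; no effect of the cap on apnea per day.

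**Step 1: closed form, all readings counted, no covariates.** Readings per day = 4(1 + p·k). With equal apnea per day in both arms, the rate ratio per reading (cap / no cap) is

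(1 + p_control·k) / (1 + p_cap·k).

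| Out of range, control v cap | k = 1 | k = 2 | k = 3 |
|---|---|---|---|
| 45% v 35% | 1.45/1.35 = 1.07 | 1.90/1.70 = 1.12 | 2.35/2.05 = 1.15 |
| 40% v 25% | 1.40/1.25 = 1.12 | 1.80/1.50 = 1.20 | 2.20/1.75 = 1.26 |
| 50% v 25% | 1.50/1.25 = 1.20 | 2.00/1.50 = 1.33 | 2.50/1.75 = 1.43 |

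The true value is 1.00 throughout. As an example, take two infants followed for 7 days with k = 2. At 50% out of range the count is 28 + 14 × 2 = 56 readings; at 25% it is 28 + 7 × 2 = 42. The same number of apneas gives rates that differ by 56/42 = 1.33. If the cap worsens control, the sign reverses: 25% in control v 40% with cap at k = 2 gives 1.50/1.80 = 0.83. With k = 0 or equal shares the ratio is 1.00.

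**Step 2: the planned neonatal-temperature covariate.** Simulation used 300 infants, stays of 2 to 7 days, 0.3 apneas a day in both arms unrelated to temperature, at most 5 re-readings per trigger, and 400 runs per scenario. The model was a Poisson regression on arm, with or without the infant's mean temperature, and with the log of all readings as offset. Hospital, the other covariates and the maternal trigger were not simulated.

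| Assumed effect of the cap | Rate ratio without covariate | Rate ratio with covariate | Runs with p < 0.05, with covariate |
|---|---|---|---|
| Mean +0.1 / +0.2 / +0.3 °C | 1.09 / 1.19 / 1.27 | 1.00 / 1.01 / 1.03 | 4–7% |
| Mean +0.3 °C, into hyperthermia | 0.78 | 0.98 | 8% |
| Mean shift and lower variability | 1.23 | 1.12 | 18% |
| Mean shift and faster return to range | 1.53 | 1.27 | 64% |
| Same mean, lower variability | 1.26 | 1.28 | 69% |
| Same mean, faster return to range | 1.48 | 1.45 | 95% |

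In the last four rows the covariate was the mean of the scheduled readings. Using the mean of all readings instead gives 1.11, 1.23, 1.26 and 1.34.

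**Step 3: time as the offset.** With log(days), the null ratio was 0.995 to 1.005 in every scenario, and 3.5% to 7% of runs fell below 0.05 (Monte Carlo error about 1 point). In the mean-shift scenarios, where it was also tried, the log of scheduled readings did equally well: it is log(4 × days), which differs from log(days) by a constant.

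**The case against.** **Only the scheduled readings may be meant.** The measurement schedule is 6-hourly wherever it is described as data collection. Data collection refers back to the outcome sections, which mention only that schedule, and the hourly readings appear only as part of the response to an abnormal temperature. The length-of-stay purpose also fits a fixed four a day. On that reading the offset is equivalent to log(days) and the bias disappears. This stands as a possible intent. But the Statistical analysis section does not say so, and taken literally its wording includes every reading.

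**The temperature covariate corrects for it.** This stands in part. For a pure shift in mean temperature, almost nothing is left. It does not hold when the cap narrows the spread or shortens excursions, and a cap meant to keep infants within a two-sided range could do either. A partial correction that comes by chance, through a covariate measured after randomization, is not a reason to keep the offset.

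**Stronger readings that the protocol does not support.** A reader might infer that readings stop when KMC stops while apneas go on being counted. An infant leaving KMC on day 3 of 7 would then have its rate overstated 7/3 = 2.3-fold. No section says that apnea is counted after KMC ends, and the figure describes one hypothetical infant. It would bias the comparison only if the cap changed how long KMC lasts. Nor does the protocol describe round-the-clock surveillance by staff; it says only that mothers are trained to watch the baby during KMC. The point needs neither claim.

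**Conclusion.** The point holds in conditional form. The offset stated for apnea is the wrong kind of denominator, and as worded it can depend on treatment through temperature. Whether it biases the result turns on whether the hourly re-readings are counted.

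- If they are, the null rate ratio before covariates is about 1.07 to 1.43, for 40–50% out of range in control against 25–35% with cap and 1 to 3 re-readings each. With the planned neonatal-temperature covariate, entered as each infant's mean, it is about 0.98 to 1.03 for a pure mean shift. It is about 1.1 to 1.45 when variability or recovery time also changes, or changes alone.
- If only scheduled readings over the apnea counting period are used, there is no bias.

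A reader might take 1.43 as the bias of the planned analysis, or conclude that any cap effect on temperature must distort the apnea result. Neither follows. The upper figure leaves out a planned covariate, all out-of-range shares and re-reading counts are assumed, and the scheduled-only reading is open. This is a secondary outcome, but the better offset is correct under either reading and costs almost nothing, so the change should be made.

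**What to change.** In the apnea model, replace the measurement-count offset with the log of observed time: days or hours from randomization to discharge, death or day 7, whichever comes first. Count apnea episodes over exactly that period and state the period in the text. Keep a reading-count denominator for the temperature outcome only.

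At minimum, state that the offset counts only scheduled 6-hourly readings, over the same period in which apneas are counted.

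The cost is one or two sentences in the Statistical analysis section. Randomization and the time of discharge or death are already needed for the trial (the Abstract lists age at discharge as an outcome), so no new data or patients are required. If apneas were recorded only as a total over the whole stay, let the observed time run to discharge or death so that the two still match.
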